## **Follow up**

The follow-up period is 6 months. Within this period recurrences requiring surgery are registered together with any complications and mortality rate of the participants. At 2 months after surgery a CT-scan is performed to assess any residual hematoma. At 6 months after surgery HRQL will be assessed using the EQ-5D questionnaire, mailed to each participant. Any loss to follow up will be recorded.

### *Indication for reoperation*

This is based on usual clinical practice and is consequently a decision made by the treating physician, often the neurosurgeon who is on-call. The indication for reoperation is typically based on the presence of significant residual or recurrent neurological symptoms (headache, paresis, dysphasia, etc.). If symptoms are present, a CT-scan is performed and if there is cSDH causing mass effect correlating with the symptoms the patient will undergo reoperation.

## **Sample size calculations**

The total number of patients will be 496 (248 in each group, respectively) for a power of 80 %. The calculation is based on a retrospective pilot study performed at Sahlgrenska University Hospital, 2013-14, with a 5 % versus 12 % recurrence rate when comparing irrigation with body-temperature fluid versus room-temperature fluid, respectively. A p-value of < 0.05 is considered statistically significant. To compensate for a loss to follow-up, we aim to include a total of 600 patients. Each centre will recruit 200 study participants ensuring homogenous recruitment between the participating centres. Although we do not anticipate a large loss to follow-up regarding the primary endpoint, we believe that this may be the case for the secondary endpoints. Thus, we will mainly compensate for a loss to follow-up regarding the secondary outcome measures such as EQ-5D 3L.

## **Data management and statistical analysis**

A statistician blinded for treatment assignments will perform the analysis according to the intention to treat principle.

The primary endpoint (rate of recurrences requiring surgery within 6 months) will be analysed using  $\chi^2$ -test for frequency comparison.

Secondary endpoints will be analysed using appropriate statistics. Categorical data will be compared using  $\chi^2$ -test or Fishers exact test. Normally distributed numerical data will be analysed using t-test and Mann Whitney U-test if skewed.

Data will be collected the CRF and on password protected computers. CRF and consent forms are stored in locked rooms at each department. Each study participant's documents are identified by the randomization number, ensuring confidentiality.

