## **Hypothesis**

The intraoperative use of irrigation fluid at body temperature results in lower recurrence rates when compared to irrigation fluid at room temperature. Consequently, the defined null hypothesis will be that there is no difference between the treatment groups.

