## **Methods**

### **Study design**

A multicentre randomised controlled trial (RCT) evaluating the use of irrigation fluid at body temperature, 37°C, versus irrigation fluid at room temperature in burr hole evacuation of cSDH. Except from random allocation of treatment between irrigation fluid temperatures the management of the participants will not differ from the current management of patients treated for cSDH. A 1:1 block randomization will be performed at each clinic.

Participating sites are the neurosurgical departments at Sahlgrenska University Hospital (Gothenburg, Sweden), Karolinska University Hospital (Stockholm, Sweden) and the Uppsala University Hospital (Uppsala, Sweden).

The primary endpoint of the study is the recurrence rate within a 6-month follow up period. Secondary endpoints include mortality rate, complication profile and frequency and health related quality of life at follow-up.

The study is registered in *clinicaltrials.gov* and reported according to the SPIRIT guidelines for reporting a RCT study protocol.  
Trials registration: ClinicalTrials.gov, NCT02757235. Registered 05/02/2016.

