## **Baseline variables**

Variables will be documented in the case report form (CRF) preoperatively, intraoperatively and within 24 hours postoperatively by the attending neurosurgeon.

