### Preoperative variables:

- Age, sex, limb weakness, Glasgow Coma Scale (GCS), disorientation, seizures, dysphasia, headache, gait disturbance, mid-line shift, maximal width of the hematoma on CT and presence of uni- or bilateral cSDH. Concomitant medication will also be recorded for aspirin, clopidogrel, warfarin and new oral anticoagulants (NOACs). Dexamethasone use will not be recorded since it is not used in the treatment of cSDH in Sweden.

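### The primary chi-square test ignores the centre blocks used to randomise and the recorded preoperative variables: valid, but a small gain in efficiency is left unused

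*Protocol*

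**What the plan says.** - **Allocation** (Protocol, Study design): "A 1:1 block randomization will be performed at each clinic". There are three neurosurgical departments. Randomization and blinding provides 200 envelopes per centre, and Sample size calculations plans 200 patients per centre.
- **Primary test** (Protocol, Data management and statistical analysis): "The primary endpoint (rate of recurrences requiring surgery within 6 months) will be analysed using" a chi-square comparison of frequencies, by intention to treat. No stratification factor or covariate is named.
- **Data available before allocation** (Protocol, Preoperative variables): age, sex, neurological status and antithrombotic drugs, together with "mid-line shift, maximal width of the hematoma on CT and presence of uni- or bilateral cSDH".
- **Sizing** (Protocol, Sample size calculations): "The total number of patients will be 496 (248 in each group, respectively) for a power of 80" per cent, based on "5 % versus 12 % recurrence rate when comparing irrigation with body-temperature fluid versus room-temperature fluid". The significance rule is "A p-value of < 0.05 is considered statistically significant".
- **Centre differences** (Protocol, Discussion): technique is described as nearly the same everywhere, while small differences between surgeons and centres are not ruled out.

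**The concern.** An analysis should normally reflect the restrictions placed on the randomisation. Blocking within centre makes the arms more alike in centre mix than simple randomisation would. A test that ignores centre does not take credit for this, so it is slightly conservative if recurrence differs between centres. Centre differences are plausible: the endpoint is a reoperation, and the protocol leaves that decision to the treating physician under usual practice.

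The same argument applies to any preoperative variable that predicts recurrence. Only about 42 to 51 recurrences are expected, so a chance imbalance in such a variable could blur the comparison, and a purely crude primary test leaves only an adjustment chosen afterwards. The interim analysis compares recurrence between the arms, so the choice is most credible if it is made before those data are seen. At stake is some attainable power and a cleaner link between design and analysis.

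**Working it through.** **1. Reproduce the planned sample size.** Inputs from the protocol: p1 = 0.05, p2 = 0.12, alpha = 0.05, power 80%. Sidedness is not stated with the sample size. The Hypothesis section says "the defined null hypothesis will be that there is no difference between the treatment groups", and two-sided is the reading that reproduces the figure.

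Formula for an uncorrected chi-square with pooled variance under the null:

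n per group = [1.960 × √(2 p̄(1 − p̄)) + 0.842 × √(p1(1 − p1) + p2(1 − p2))]² / (p2 − p1)²

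- p̄ = (0.05 + 0.12)/2 = 0.085, and √(2 × 0.085 × 0.915) = 0.3944
- √(0.0475 + 0.1056) = 0.3913
- n = (0.7730 + 0.3293)² / 0.07² = 1.2151 / 0.0049 = 247.98, so 248 per group and 496 in total

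This matches the protocol exactly. The sample size belongs to the same crude test that the analysis section names.

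**2. Power of the crude test at full recruitment.** At 300 per group: (0.07 × √300 − 0.7730)/0.3913 = 1.123, which gives power of 86.9% (88.2% by exact binomial calculation). At 248 per group the formula gives 80.0% (exact 81.2%).

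**3. Expected events.** 0.085 × 496 = 42 and 0.085 × 600 = 51.

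**4. What stratification or adjustment adds.** Simulation with 4,000 trials per scenario: three equal centres, 1:1 within centre, overall rates held at 12% and 5%.

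The protocol gives no between-centre spread and no prognostic strength, so both are **assumptions**. Centre log-odds shifts were 0, ±0.5 or ±1.0. One preoperative score had a log-odds SD of 0, 0.5 or 1.0. With no score, the centre rates in the room-temperature arm that average 12% are about 7/11/17% for shifts of ±0.5 and 4/10/23% for ±1.0.

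Power (%) at 498 patients:

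| Centre shift | Score SD | Crude | CMH by centre | Logistic: centre + score |
|---|---|---|---|---|
| 0 | 0 | 80.7 | 80.8 | not run |
| 0 | 0.5 | 81.1 | 81.2 | 81.0 |
| 0 | 1.0 | 80.6 | 80.6 | 83.2 |
| ±0.5 | 0 | 81.3 | 81.5 | not run |
| ±0.5 | 0.5 | 81.5 | 81.8 | 81.6 |
| ±0.5 | 1.0 | 80.7 | 80.9 | 83.6 |
| ±1.0 | 0 | 82.4 | 83.5 | not run |
| ±1.0 | 0.5 | 81.9 | 82.9 | 83.2 |
| ±1.0 | 1.0 | 81.2 | 82.5 | 85.2 |

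Gain over the crude test on the same simulated trials, from unrounded results:

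- CMH by centre: 0.0 to 0.1 points with no centre differences, 0.2 with shifts of ±0.5, and 1.0 to 1.3 with ±1.0.
- Logistic model with centre and score: −0.2 to +1.3 points at score SD 0.5, and +2.6 to +4.1 at SD 1.0.
- At 600 patients: −0.1 to +0.6 points for CMH, and 0 to 2.9 for the logistic model.

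**5. Validity.** With both arms at 8.5%, the crude test rejected in 4.1% to 5.5% of trials across all scenarios at both sizes. The Monte Carlo standard error is √(0.05 × 0.95/4000) = 0.3 points, so there is no sign of inflation. One power figure has a standard error of about 0.6 points. The gains compare tests on the same data sets, so they are less noisy than that.

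**The case against.** The strongest reply is that nothing is broken. Test and sample size agree, type I error is held, and at 600 patients the crude test has about 87% power with no large loss expected for the primary endpoint. The point best grounded in the document, that centre is used to randomise but not to analyse, is worth about one power point at most, and that needs a centre spread for which the Discussion gives no support. The larger gain needs a prognostic strength that the protocol does not give. All of this stands, and it sets the size of the point.

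A reader might infer more than the document supports:

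- **That planned power is lost.** It is not. The stated 80% was computed for the crude test, so what is forgone is possible extra power.
- **That the preoperative variables are known predictors of recurrence.** The protocol calls none of them prognostic. Their value is an assumption here.
- **That these data go unused altogether.** The SAP is not shown and may contain supportive adjusted analyses. Only the named primary test is at issue, and that is fixed in the protocol.
- **That counting a bilateral patient once is an error.** The patient is the randomised unit and both sides get the same fluid, so counting once is right.
- **That the Baseline variables section plans adjustment for data collected after allocation.** It says "Variables will be documented in the case report form (CRF) preoperatively, intraoperatively and within 24 hours postoperatively", but the three sets are listed separately and no adjustment for any of them is planned.

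What remains against leaving the plan unchanged is that the mismatch between allocation and primary test is stated in the protocol itself and is nearly free to remove.

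**Conclusion.** The point holds as a modest improvement in design consistency and efficiency. The protocol randomises within three centres and fixes a primary test that uses neither centre nor any preoperative variable. That test is valid and meets its stated power.

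The expected gain at about 498 patients is 0 to 1.3 power points from centre alone and about 0 to 4 points with covariates. At 600 patients it is at most about 0.6 and 2.9 points. The upper ends assume centre log-odds shifts of ±1.0 and, for covariates, a score with log-odds SD 1.0. With a weak score (SD 0.5) the covariate gain is close to nil unless centres differ widely. The mismatch is certain from the text, but the size of the benefit is not.

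**What to change.** Change the primary analysis in one of two ways, before the interim analysis:

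1. **Minimum:** a Cochran-Mantel-Haenszel test stratified by the three centres.
2. **Fuller:** a logistic model with treatment, centre and a short fixed list of preoperative covariates, for example bilateral cSDH, antithrombotic use and maximal hematoma width. Report the effect as a standardised risk difference with 95% CI, so that it stays on the scale of the 12% versus 5% planning rates.

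Keep the crude chi-square as a supportive analysis, since it is the test the sample size was built on. The sample size need not change.

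**Cost:** a sentence in the protocol and the SAP, a little more analysis work, and a simple rule for the rare missing baseline value. No new data are needed. With about 42 to 51 expected events the model has room for only a few covariates, so the list must stay short.

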## **Data monitoring**

An interim analysis will be performed by an independent statistician when each site has 100 subjects with a completed 6 month follow up. The interim analysis will focus on differences in mortality and recurrence rates (the primary endpoint) between study groups. In addition, each site will cross monitor each other regarding obtained consents and source of clinical data.

## **Ethical approval**

The study has been approved by the Regional Ethics Committee in Gothenburg, Sweden, January 19, 2016 (reference number: 932-15).

## **Discussion**

To the best of our knowledge this is the first randomised controlled trial comparing irrigation fluid temperatures used during surgical evacuation of chronic subdural hematomas. Chronic subdural hematoma is an increasingly common condition affection the elderly, believed to be linked to demographic changes, extensive use of anticoagulants/anti-platelet therapy and easy access to radiological examination of the brain. The recurrence rate is rather high, with a need for randomized controlled trials in an effort to optimize treatment strategies in hope of reducing the recurrence rates. A possible variable influencing the recurrence rate is the temperature of the irrigation fluid used during hematoma evacuation, by affecting solubility of the hematoma and/or coagulation. To test this theory, the current study was initiated.

If a decreased recurrence rate is observed in this multicenter randomized controlled trial, a new surgical standard of irrigation temperature can be established. If the need of reoperation could be diminished this has obvious gains both for the patient and the health care system.

Strengths of the study include the RCT setup and the involvement of three independent neurosurgical centers in Sweden, covering 60 % of the Swedish population. All of these with population-based catchment areas and almost identical surgical technique. Also, a digitalized patient chart system ensures easy access facilitating follow-up. Limitations include the inability to blind the treating surgeon at to the temperature of the irrigation fluid, generating possible bias. Furthermore, although the surgical strategy is very

homogeneous among the participating centers, subtle differences in the surgical method between individual surgeons and also between the centers cannot be excluded.

[figure not shown]

Figure 1: SIC-study flowchart

## List of abbreviations

cSDH: chronic Subdural Hematoma  
 RCT: Randomized Controlled Trial  
 HRQL: Health Related Quality of Life  
 CRF: Case Report Form  
 ICU: Intensive Care Unit  
 GCS: Glasgow Coma Scale  
 SPIRIT: Standard Protocol Items: Recommendations for Interventional Trials

## Declarations

**Ethics approval and consent to participate**

347  
348 The regional ethical review board of Gothenburg, Sweden, reviewed the project and the  
349 study was approved January 19, 2016 (reference number: 932-15).  
350  
351  
352  
353  
354  
355  
356  
357  
358  
359  
360  
361  
362  
363  
364  
365  
366  
367  
368  
369  
370  
371  
372  
373  
374  
375  
376  
377  
378  
379  
380  
381  
382
